## Abstract

**Background:**

Data from High Income Countries have now linked low nurse staff to patient ratios to poor quality patient care. Adequately staffing hospitals is however still a challenge in resource-constrained Low-middle income countries (LMICs) and poor staff-to-patient ratios are largely taken as a norm. This in part relates to limited evidence on the relationship between staffing and quality of patient care in these settings and also an absence of research on benefits that might occur from improving hospital staff numbers in LMICs. This study will determine the effect on the quality of patient care of prospectively adding extra nursing staff to newborn units in a resource constrained LMIC setting and describe the relationship between staffing and quality of care.

**Methods:**

This prospective workforce intervention study will involve a multi-method approach. We will conduct a before and after study in newborn units of 4 intervention hospitals and a single time-point comparison in 4 non-intervention hospitals to determine if there is a change in the level of missed nursing care, a process measure of the quality of patient care. We will also determine the effect of our intervention on routinely collected quality indicators using interrupted time series analysis. Using three nurse staffing metrics (Total nursing hours, nursing hours per patient day and nursing hours per patient per shift), we will describe the relationship between staffing and the quality of patient care.

**Discussion:**

There is an urgent need for the implementation of staffing policies in resource constrained LMICs that are guided by relevant contextual data. To the best of our knowledge, this is the first study to evaluate the prospective addition of nursing staff in resource-constrained care settings. Our findings are likely to provide the much-needed evidence for better staffing in these settings.

**Trial registration:**

This study was retrospectively registered in the Pan African Clinical Trial Registry (https://pactr.samrc.ac.za/Default.aspx?Logout=True) database on the 10th of June 2022 with a unique identification number-PACTR202206477083141.

**Supplementary Information:**

The online version contains supplementary material available at 10.1186/s12913-022-08597-9.

## Background

Nurses represent the largest group within the health workforce and are the backbone of health service delivery [1]. As a result, they are critical to maintaining a healthy population and for the attainment of all global development goals that relate to quality and equitable health care [1]. To underscore the important role nurses play in the global health agenda, the 74^th^ World Health Assembly designated the year 2020 as the International Year of the Nurse and the Midwife [2].

Despite being indispensable to health systems around the world, there is still a global shortage of nurses; 90% of which occur in resource-constrained LMICs resulting in extreme nursing staff-to-patient ratios that compromise the quality of patient care provided [3, 4]. These shortages cut across all sectors of the health system including the care of more vulnerable groups such as pregnant women and newborns. Human resource for health (HRH) shortages are viewed as an important factor responsible for the untimely deaths of mothers and their newborns while receiving care [5]. In addition to HRH challenges, resource-constrained settings have wider challenges with the infrastructure and material resources needed to provide quality care.

Globally, evidence on the role nurse staffing plays in ensuring the quality of patient care has largely come from High-income Countries (HICs), mainly ecological analyses of administrative health data or cross-sectional studies that are based on nurse self-report data [6–11]. These HICs have distinctly different organisational and patient care contexts to LMICs. They particularly have a better nurse to patient ratios, so there is limited evidence on nurse staffing and quality of care relationships from areas with ratios typical of LMIC contexts. The predominance of non-interventional research also limits causal inference in this research area and it is suggested that hospital-level ecological analysis might not reflect the variability occurring at lower levels of care [12, 13]. Well-designed patient-level analysis of data might provide more information on the role of nurse staffing in ensuring quality patient care, particularly in LMIC contexts where there is limited data.

Research relating nurse staffing and quality of care has largely employed outcome-based quality indicators, for example, mortality and length of hospital stay, with less work on process-based indicators that provide the link between nurse staffing and health outcomes [14]. Process-based indicators may be a more sensitive means to explore whether interventions or exposures have plausible effects. An increasingly studied process measure of quality is missed nursing care; an umbrella term that describes gaps in nursing care provision and can involve partially omitted, completely omitted or delayed clinical, emotional and administrative nursing duties [15, 16]. The study of this phenomenon has, however, largely been based on nurses self-reporting with well-known limitations of recall and social desirability bias. Ethically acceptable interventional designs that evaluate the effects on missed care based on direct observation would be an advantage.

The current study proposes to evaluate the effects on nurse-delivered care of a prospectively designed workforce intervention aimed at improving nurse staffing in select neonatal units in Kenya. The primary outcome, missed nursing care, a process-based measure of the quality of patient care will be assessed at the patient level using direct observation of care [17].

### Hypothesis

We hypothesize that adding extra ward nurses to neonatal units in Kenya will result in improvements in the process of care (decreased level of missed nursing care).

## Methods/design

### General aim

To evaluate if and how an intervention to improve neonatal ward nurse staffing levels in a resource constrained LMIC setting results in improvements in the quality of patient care provided.

### Objectives

#### Primary objective

To determine the effect of enhancing nurse staffing on missed nursing care measured using the nursing care index (NCI) tool in a before and after design study of four hospitals.

#### Secondary objectives

2.To examine the degree to which additional staff affects nurse staffing metrics on Kenyan newborn units, as a measure of intervention fidelity, and the relationship between these metrics and missed nursing care on these wards.

#### Pre-specified observational evaluation

3.To track changes in neonatal quality indicators derived from routinely collected data across 12 hospitals and explore differences between hospitals receiving additional staffing and those that do not.

### Research setting

This project will be introducing supplemental nurses to resource-constrained neonatal units in four hospitals aiming to offer intermediate-level neonatal care in Kenya which all belong to a Clinical Information Network (CIN). Briefly, the CIN is a learning health system that has been in existence since 2013 and spans 23 Kenyan hospitals where routine paediatric and newborn admission data are collected using structured data collection tools [18]. The information from the CIN provides feedback to the participating hospitals on the overall quality of care being provided but has also served as a platform for research on patient care quality and to assess interventions targeting better paediatric and newborn care [18]. Twelve of the 23 CIN hospitals received a bundle of neonatal technologies (phototherapy machines, Continuous Positive Airway Pressure devices, pulse oximeters and oxygen concentrators) provided by the Newborn Essential Solutions and Technology 360^o^ (NEST-360°) programme before the end of 2021 [19].

### Study design

This study will employ a prospective, multimethod approach to evaluate if an intervention to improve nurse staffing in Kenyan intermediate-level neonatal wards improves nurse-delivered care.

#### Primary and secondary objective (how supplemental nurse staffing impacts the level of missed nursing care)

Using bedside observations of care, we will employ a before and after design in 4 intervention hospitals selected from the 12 NEST360 hospitals. Our baseline observations will be conducted in the 4 intervention hospitals before enhancing nurse staffing and additional observations will be performed after 6 months. At the same post-intervention time point observations will be made in a further set of 4 hospitals from the original 12 that have not received the workforce intervention (Fig. 1). Our primary analysis will be the before-and-after within-site comparison, the single time-point observations in the 4 non-intervention sites will serve as an external reference for our 4 intervention hospitals. Data on nurse staffing metrics will be collected for 6 months before the workforce enhancement and in the 6 months leading to the post-intervention assessment in the 4 intervention hospitals. These data will be used to assess whether and to what degree providing additional nurses changes nurse staffing metrics as an indication of intervention fidelity. Similar data on nurse staffing metrics will be collected from the 4 reference hospitals and then data from all 8 hospitals at the post-intervention time point will be used to address our secondary objective of exploring the relationship between nurse staffing metrics and nurse-delivered care.

**Fig. 1 Fig1:**
[figure not shown]
Timeline for data collection for the workforce intervention study. ^&^10 months is retrospective data collection 12 months before introducing supplemental nurses to intervention units

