#### Observational evaluation

We will use data from the 12 NEST360 hospitals (spanning the 4 intervention hospitals and 8 non-intervention hospitals) to track a set of secondarily collected quality indicators using CIN data for 12 months before and 12 months after the 4 intervention hospitals receive additional nurses. Potential intervention effects will be explored using interrupted time series analysis (Fig. 1).

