##### Observational objective

For our secondary quality of care indicator analysis, our study population will be all neonates admitted to our 4 study facilities and a set of 8 non-intervention hospitals, 12 months before and 12 months after introducing supplemental newborn unit nurses. For this population, we will track the number of vital signs conducted in the first 48 h of admission and the change in newborn mortality. This data is available from the CIN database.

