## Discussion

Both material and human resources are crucial to maintaining the quality of patient care. Interventions to improve in-patient quality of care in resource-constrained settings have largely ignored a critical element for quality service delivery which is having an adequate number of health staff. For example, many interventions focus on enhancing technology or skill acquisition of existing local health workers. Yet, these require the presence of a sufficient numbers of staff to promote optimal effectiveness and ensure patient safety.

To the best of our knowledge, this is the first prospective workforce intervention study that proposes to supplement nurses within a hospital setting to examine the association between improved staffing and quality of care. Previous research has been retrospective, evaluating the effects of improvements in staffing in the form of natural experiments or has involved prospective supplementation of nursing assistants [25–27].

We recognise that the Hawthorne effect is a limitation of studies that involve direct observations [28], and we plan to minimise the effect of this on our data collection. Similar to our earlier work using the NCI tool, before the current data collection, we will conduct training of the observers and have a one-week familiarisation period within our study sites [17]. This period involves observers learning the layout and routines of each unit and this also serves to make the nurses within the units comfortable with the observer. We will spread our data collection across randomly selected 12-h nursing shifts over 5 to 6 weeks that are not known to the nursing staff in advance while evidence also suggests that following the continuous presence of an observer for longer periods, the Hawthorne effect is likely to diminish [29].

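### Bedside observers are present before the intervention only in the 4 intervention hospitals, so the exploratory vital-sign time series may be lifted unequally between groups and understate the nurse effect

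*Protocol article*

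**What the plan says.** Study design, under the primary and secondary objective, sets the observation schedule: "Our baseline observations will be conducted in the 4 intervention hospitals before enhancing nurse staffing and additional observations will be performed after 6 months". It continues: "At the same post-intervention time point observations will be made in a further set of 4 hospitals from the original 12". So all 4 intervention hospitals are observed twice, 4 non-intervention hospitals once, and the remaining 4 never.

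The Observational evaluation section plans an interrupted time series in all 12 hospitals, "using CIN data for 12 months before and 12 months after the 4 intervention hospitals receive additional nurses". The matching objective is to "explore differences between hospitals receiving additional staffing and those that do not". Under the observational objective of the Study population section, the indicator is described as follows: "we will track the number of vital signs conducted in the first 48 h of admission". Mortality is the other outcome. The Outcomes section makes clear that the vital signs are those recorded by the unit's own nurses, and says that an improvement coinciding with the added staff would support the staffing hypothesis.

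The Discussion takes up reactivity: "We recognise that the Hawthorne effect is a limitation of studies that involve direct observations". It answers with a familiarisation week and with unannounced, randomly chosen shifts over 5 to 6 weeks. Both concern the bedside data.

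The Fig. 1 legend notes that "10 months is retrospective data collection 12 months before introducing supplemental nurses to intervention units". The figure itself is not available here.

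**The concern.** The nurses who are watched for the NCI also produce the vital-sign records in the time series. If they chart more while observers are on the unit, some months of the series are not usual care.

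The schedule spreads those months unevenly. In the pre-period they occur in the intervention hospitals and nowhere else. At 6 months they occur in 4 of 4 intervention hospitals and 4 of 8 others. If the pre-period exposure lies close to the start of the intervention, it raises the end of the pre-intervention line. The projection against which the nurse effect is read then becomes too high and too steep. The non-intervention hospitals have no matching exposure, so subtracting their series does not cancel it. At stake is a true improvement in vital-sign monitoring that appears smaller than it is, in the analysis meant to support the staffing hypothesis.

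**Working it through.** **The plan's own figure.** The protocol gives no design figure for the time series. Its only one is 213 babies per period for the NCI. This reproduces: 2 × [15 × (1.960 + 0.842) / 5]² = 141.3, rounded up to 142, and 142 × 1.5 = 213. The point does not rest on it.

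**Inputs.**
- 12 pre- and 12 post-intervention months; 4 intervention and 8 other hospitals (Observational evaluation).
- Observation schedule (Study design).
- 1 + 5 to 6 = 6 to 7 weeks on site per round (Discussion).
- 55 babies per hospital per period, 4 per shift, 12-hour shifts (Statistical power).
- Assumptions: observers in pre-months 11–12 (or 12 only) and around months 18–19 (or 18 only) of the 24; independent errors; true nurse effect zero; indicator raised by d in each observer month.

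**Weights.** The model has an intercept, a slope, a level change at month 13 and a slope change. With 12 points on each side, the sum of squares of time about its mean is 12 × (12² − 1) / 12 = 143. The weight of month t is:
- level change, pre: −[1/12 + 6.5 × (t − 6.5)/143]; post: 1/12 − 5.5 × (t − 18.5)/143
- slope change, pre: −(t − 6.5)/143; post: (t − 18.5)/143

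| Month | Level change | Slope change |
|---|---|---|
| 11 | −0.288 | −0.0315 |
| 12 | −0.333 | −0.0385 |
| 18 | +0.103 | −0.0035 |
| 19 | +0.064 | +0.0035 |

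Month 12 has the largest absolute level weight of all 24 months.

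**Single-arm bias, in units of d.** The effect at post-month 6 is level + 5 × slope; at post-month 12 it is level + 11 × slope.

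| Observer months | Level | Post-month 6 | Post-month 12 |
|---|---|---|---|
| 11, 12, 18, 19 | −0.45 | −0.80 | −1.22 |
| 12, 18 | −0.23 | −0.44 | −0.69 |
| 10, 11, 18, 19 | −0.36 | −0.64 | −0.98 |
| 9, 10, 18, 19 | −0.27 | −0.48 | −0.73 |

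First row: −0.288 − 0.333 + 0.103 + 0.064 = −0.45; slope −0.0315 − 0.0385 − 0.0035 + 0.0035 = −0.070; −0.455 − 11 × 0.070 = −1.22.

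**Between-group contrast.** Half of the non-intervention hospitals are observed at 6 months, so their average level change shifts by 0.5 × (0.103 + 0.064) = +0.08d. The net level bias is −0.455 − 0.083 = −0.54d. With the 6-month round in months 19–20 it is −0.58d.

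**How large d might be.** 55/4 is about 14 observed shifts per hospital. Five to six weeks contain 70 to 84 shifts, so 14/84 = 17% to 14/70 = 20% are observed. Take, as an assumption, a rise of 10 points in recording. If only observed shifts react, d is 1.7 to 2.0. The first row then gives a level bias of about −0.8 to −0.9 points, and about −2.0 to −2.4 at post-month 12. If the whole unit reacts throughout, d = 10 and the biases are about −4.5 and −12.2.

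**The case against.** The strongest objection concerns timing. The legend does not mention observers, the item it annotates cannot be seen, and the text says only that baseline observation precedes the added staff. A reader might take the legend as stating that observers were present in the last two pre-months. It does not. That placement is inferred from the roughly 2 non-retrospective months and the 6 to 7 weeks on site. Placement matters. Months 9–10 still give −0.73d at post-month 12, but in months 6–7 the pre-period level bias is only −0.17d, which the 6-month round offsets within the arm.

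Second, a reader might conclude that the series is contaminated. The documents give neither evidence nor size of an observer effect on routine charting, and they plan steps to reduce reactivity. Exposure is also thin. The series covers the first 48 hours of every admission, while each observed baby is watched for 12 hours. Even if all 55 were newly admitted, that is 55 × 12 = 660 hours against 48 hours for each of about 125 admissions (1299 × 5/52) to 290 admissions (2514 × 6/52), or roughly 11% to 5%. Nor do 6 to 7 weeks fill two months: weighting months 11 and 19 at 0.6 cuts the level bias from −0.45d to −0.36d.

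Third, an article may leave the time-series model to the analysis plan, so a missing covariate is not in itself a fault. That stands. What remains is that the schedule the article does state creates an imbalance within a comparison it also states, while its caution about observation stops at the bedside data.

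**Conclusion.** The point holds as a risk. The unequal exposure is fixed by the stated schedule; its effect on the series is not known. If observation raises routine recording and fell late in the pre-period, the nurse effect on vital signs is understated by about 0.23d to 0.45d in level and 0.7d to 1.2d at post-month 12 in a single-arm analysis. Contrasting with the other hospitals leaves the level bias at about 0.54d to 0.58d when two months per round are affected. These figures rest on whole-month exposure, independent errors and the inferred timing. The value of d is not given, and is much smaller if only observed shifts react.

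A reader might infer that most or all of a nurse effect would be lost. The documents do not support this: the multiples apply to d, not to the nurse effect, and the largest is the projection to post-month 12. Nor does the mechanism reach the primary result, since observers are present in both NCI periods. The affected analysis is exploratory, and the bias would hide a benefit, not create one. This calls for a modest safeguard.

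**What to change.** Pre-specify one sensitivity analysis of the time series. Add a hospital-by-month indicator for study observers present, covering the familiarisation and observation weeks (as a fraction where a round fills only part of a month), or drop those hospital-months. State the calendar months of each observation round so that the exposure can be seen, and extend the Discussion's caution about observation to the vital-sign series.

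No new data are needed, because the team knows its own observation calendar. The cost is precision. With observers in months 11–12 and 18–19, the indicator multiplies the SE of the level change by about 1.06 and that of the slope change by about 1.06. Dropping those months multiplies them by about 1.27 and 1.17. The indicator is cheaper because it assumes the same observer effect in both rounds; dropping the months avoids that assumption.

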#### Observational evaluation

We will use data from the 12 NEST360 hospitals (spanning the 4 intervention hospitals and 8 non-intervention hospitals) to track a set of secondarily collected quality indicators using CIN data for 12 months before and 12 months after the 4 intervention hospitals receive additional nurses. Potential intervention effects will be explored using interrupted time series analysis (Fig. 1).

### Site selection and eligibility criteria

We have selected solely public district-level health facilities that are part of the CIN and that have received a standard set of neonatal equipment and linked technical training as part of the NEST360 programme as study sites. Previous research has shown that these types of public hospitals experience the greatest level of missed nursing care associated with poor staffing levels [17]. Intervention sites are selected to be within 1 to 3 h of the Kenyan Capital, Nairobi because of travel restrictions linked to the Covid-19 pandemic enabling feasible access to these research sites. Table 1 provides a comparison of the staffing numbers and average admissions for the 4 intervention sites.

**Table 1 Tab1:** Bed capacity, annual admissions, and staffing strengths across the 4 intervention hospitals

Metric	Hospital A	Hospital B	Hospital C	Hospital D
Newborn unit bed capacity^a^	53	50	38	47
Nurse staffing numbers (pre-intervention)	17	11	10	8
Expected percentage change in nurse staffing after adding 3 extra nurses (%)	17.6	27.3	30.0	37.5
**Number of other staff**				
Consultant Paediatricians	2	2	2	2
Medical officers	0	0	1	2
Medical interns	2	2	2	2
Ward clerks	3	3	1	1^b^
Average annual neonatal admissions^c^	2357	2514	1299	1800

^a^In practice, there is cot and incubator sharing and admissions out-strip the bed capacity

^b^Shared with other units

^c^2019/2020 data from a NEST-360 baseline facility assessment

#### Study population

##### Primary objective 

For our research on missed nursing care, we will recruit eligible newborn infants admitted to newborn units in selected hospitals for observations of care. We plan to recruit babies across all illness severity categories as our primary outcome, missed nursing care is associated with illness severity categories [17]. Babies for observation will be identified from previously defined categories in use in Kenyan newborn units; categories, A, B and C, where categories A are the most acutely ill babies, B are moderately ill and C are stable babies [20].

